### Randomization, Allocation, and Blinding

Randomization will be performed using IBM SPSS Statistics 27.0 and manual assistance. Prior to the study, a randomization specialist will be assigned to generate a random set of numbers based on numbers 1-96 using IBM SPSS Statistics 27.0. After the numbers are sorted from small to large, the 96 cases will be randomly divided into the intervention group and the control group, and the numbers and corresponding groups will be sent to the researchers. Recruited patients who meet the inclusion criteria will be listed in a table and numbered in order of enrollment. The current caseload will be determined according to the grouping generated by randomly assigned personnel. The lists of the 2 groups will be sorted into tables and sent to the actual operators, who will be informed of the specific methods of operation of each group. This method can reduce unnecessary communication between researchers and randomization specialists in the grouping process as far as possible in order to reduce potential bias from researchers’ subjective intentions in participant grouping.

We have established rigorous assessment protocols and guidelines. An independent assessor, blinded to participants’ group allocations and unaware of the intervention methods used for the 2 groups, will conduct all outcome evaluations. Upon completion of the study, the assessor will be requested to estimate participants’ group assignments. Subsequently, their estimations will be compared with the actual group allocations. This procedure aims to evaluate the effectiveness of the blinding process. Should any breach of blinding be identified, we will thoroughly account for it and provide a comprehensive explanation within the data analysis and interpretation of results.

Information about the existence of another intervention group will not be disclosed to the participants, and they will be strictly instructed not to disclose any information related to their intervention to the assessor.

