**Methods:**

This single-blind randomized controlled trial (RCT) will involve a total of 96 participants with KOA from 1 study center (including 2 branches). Participants will be randomly divided into a conventional treatment (control) group and a Tuina+conventional treatment (intervention) group in a 1:1 ratio. Participants in the control group will receive regular health education, self-administered acupressure, and functional exercise. This routine will be completed in 4 weeks, with a total of 5 sessions planned each week. Participants in the intervention group will receive 8 sessions of Tuina therapy based on hip-knee-ankle synergy (twice a week for 4 weeks), combined with conventional treatment. The primary outcome of this study will be improvement in WOMAC (Western Ontario and McMaster Universities Osteoarthritis Index) scores from baseline to 16 weeks. Among the secondary measures, the Key Symptoms and Signs/TCM Syndrome Classification Quantitative Evaluation of KOA and the 11-item Tampa Scale of Kinesiophobia (TSK-11) score will be evaluated from baseline to 16 weeks. The Functional Movement Screen (FMS), the Timed Up and Go (TUG) test, and the Weight Bearing Lunge Test (WBLT) scores will only be evaluated at baseline and 4 weeks.

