### Participants

All participants will be recruited from among patients with KOA visiting Shuguang Hospital affiliated with the Shanghai University of Traditional Chinese Medicine. Patients will first be enrolled based on their basic information, medical history, X-ray results, and WOMAC (Western Ontario and McMaster Universities Osteoarthritis Index) scores. Patients who are willing to participate in this trial and demonstrate an understanding of the objectives and methods of the study by providing signed informed consent will then be randomly assigned to 2 groups: a conventional treatment (control) group and a Tuina+conventional treatment (intervention) group.

At baseline, some information will be collected in order to account for potential confounding variables, including basic information (name, sex, age, height, weight, telephone number, profession). We will calculate the patients’ BMI using their height and weight. Physical activity levels will be assessed and recorded using a 3-tier classification (light, moderate, and vigorous). Additionally, we will document the types of comorbidities and medication use, including type, dosage, and frequency. These variables will be included in multivariate analyses to adjust for their potential confounding effects on pain perception and functional outcomes.

All participants will be evaluated 4 times: at baseline and at 4-, 8-, and 16-week follow-up.

The inclusion criteria are as follows:

A diagnosis of KOA according to American College of Rheumatology criteria [17]Average pain score in WOMAC≥4An abnormal lower limb line on the lower limb length X-rayThe patient’s age is 20-65 years, male or female.No other treatment in the past 4 weeks that may interfere with the results of this study

In addition, patients with unilateral KOA will be included in the study.

The exclusion criteria are as follows:

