#### Control Group (Conventional Treatment)

According to the “Basic treatment” part of the *Guidelines for TCM Diagnosis and Treatment of Knee Osteoarthritis* (2020 edition) [21], we will include health education, weight management, functional exercise, and self-administered acupressure [22]. We will distribute health education manuals, provide online and offline guidance for patients, popularize KOA-related health knowledge to patients, and help them understand the importance of daily KOA protective measures and precautions through popular science health education. In this group, patients will be taught self-administered acupressure and functional exercise once daily, 5 days/week for 4 weeks.

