#### Intervention Group (Tuina Plus Conventional Treatment)

In this group, the treatment regimen will also receive Tuina therapy based on hip-knee-ankle synergy (Figure 2). The frequency of treatment will be twice a week for 4 weeks. We have established a scientific, normative, standardized work process, operating procedures, and quality standards. All treatment will be performed by registered Tuina doctors, who have clinician qualifications and have been engaged in Tuina clinical work for more than 5 years. All of have graduated with Tuina as their major and have been trained and assessed with Tuina's standard operating procedures (SOP) for this study.

First, the patient will lie in a supine position, with legs straight and relaxed. The doctor will relax the soft tissues of the groin, thigh, knees, and lower legs in turn, including the quadriceps femoris muscle, the tibialis anterior muscle, and soft tissues around the patella. The degree of manual relaxation will be determined based on the patient’s sensation of slight soreness and distension.

Second, the patient will keep lying in a supine position. Acupressure will be administered to the points around the knee. The patella will be mobilized, and the cordage, patellar ligament, medial and lateral retinaculum, and medial and lateral collateral ligament will be relaxed. Depending on the actual situation, knee adjustment manipulation techniques in a seated or a supine position will be performed, when necessary. Next, the doctor will rub the knee and transfer heat.

Third, the patient will keep lying in a supine position. The doctor will hold the patient’s ankle with both hands and place the thumb on the lateral or medial malleolus suture and press, while the other 4 fingers will be fixed, rotating and shaking the foot several times. The ankle will be pulled outward and downward with both thumbs, and the ankle joint will be held and the lower limb stretched.

Finally, the patient will lie in a prone position, the doctor will relax the muscles of the buttocks, thighs, and calves in turn, including the gluteus maximus, gluteus medius, piriformis, biceps femoris, and gastrocnemius muscles. The handling will not be too heavy. The doctor will measure the degree of swelling and numbness. Depending on the actual situation, hip joint adjustment manipulation techniques will be performed, when necessary.

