### Safety Assessments

We will also pay close attention to adverse events. Throughout the trial period, any adverse events or phenomena observed will be carefully recorded in the designated case report form (CRF). This documentation will include the precise timing of the event, the accompanying symptoms, the severity of the condition, its duration, the therapeutic measures implemented, and the outcome. The research team will carefully analyze the correlation between adverse events and the required intervention, recording their details, signs, and precise dates for future reference.

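### The rule against telling the assessor about the intervention has no stated exception for adverse events, and harms recorded as observed may be ascertained unequally between arms

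*Protocol article*

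**What the plan says.** **Blinding.** The section Randomization, Allocation, and Blinding says of participants that "they will be strictly instructed not to disclose any information related to their intervention to the assessor". It gives no exception for symptoms or harms. The Discussion (Strengths and Limitations) repeats the instruction and offers it as one of the measures against bias from the unequal treatment dosage. The same blinding section says that the independent assessor "will conduct all outcome evaluations".

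**Visits.** Under Participants: "All participants will be evaluated 4 times: at baseline and at 4-, 8-, and 16-week follow-up".

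**Treatment contacts.** The Abstract gives the intervention arm its Tuina sessions: "Participants in the intervention group will receive 8 sessions of Tuina therapy based on hip-knee-ankle synergy (twice a week for 4 weeks"). The Intervention Group section agrees ("The frequency of treatment will be twice a week for 4 weeks") and says who delivers them: "All treatment will be performed by registered Tuina doctors". Both arms receive conventional treatment. For this the Control Group section says that staff will "provide online and offline guidance for patients", and that acupressure and exercise are taught on a once-daily, 5-days-a-week pattern for 4 weeks.

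**Harms.** Under Safety Assessments, "any adverse events or phenomena observed will be carefully recorded in the designated case report form (CRF"), for the whole trial. The research team then examines the relation of events to the intervention. The section does not say who asks about events, at which visits, or that both arms are asked alike.

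**The concern.** Two features of the plan fit poorly together.

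First, soreness or a flare after manipulation or after the prescribed exercises can fairly be read by a participant as information about the intervention. A participant who takes the instruction literally cannot tell that such a symptom may be mentioned at an evaluation visit. The safety section needs exactly that information.

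Secondly, when events are recorded as observed, the number recorded depends on how often someone is in a position to observe. The Tuina arm meets a doctor, hands-on, 8 times; the control arm has no matching sessions.

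What is at stake is the harms record of a manual therapy. If the arms are later set side by side, a difference in recorded events could partly reflect contact frequency rather than risk. Low capture after week 4 could also make both arms look safer than they are.

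**Working it through.** **1. The plan's own figure.** Tuina sessions: 2 per week × 4 weeks = 8, as the Abstract states.

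**2. Contacts after baseline, counting only evaluations and Tuina sessions.** Evaluations at weeks 4, 8 and 16 = 3 in each arm.
- Tuina arm: 3 + 8 = 11
- Control arm: 3
- Excess: 11 − 3 = 8; ratio 11/3 = 3.7

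**3. Adding the conventional treatment.** The Control Group section can be read two ways. If the teaching is supervised daily, it adds up to 5 × 4 = 20 contacts, and these are shared if both arms receive the same conventional treatment.
- Tuina arm: 11 + 20 = 31
- Control arm: 3 + 20 = 23
- Excess: still 8; ratio 31/23 = 1.35

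If patients are taught once and then practise alone, only the guidance contacts are added, and their number is not given. The absolute excess of 8 does not depend on the reading, but the relative gap does.

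**4. When the excess occurs.** All 8 extra contacts fall in weeks 1 to 4, and the Abstract says the conventional routine is also completed in 4 weeks. For the remaining (16 − 4)/16 = 75% of follow-up, the only scheduled contacts stated are the evaluations at weeks 8 and 16. These are the same in both arms and fall under the non-disclosure instruction. So the difference between arms comes from weeks 1 to 4, and the later weeks raise a question of low capture in both arms.

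**5. Direction, by illustration.** Assume that an existing event is recorded at each contact independently with probability p, so that capture over k contacts is 1 − (1 − p)^k. The document gives no p; the values below are assumptions.

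| p | 3 contacts (control) | 11 contacts (Tuina) | 23 contacts (control) | 31 contacts (Tuina) |
|---|---|---|---|---|
| 0.05 | 14% | 43% | 69% | 80% |
| 0.10 | 27% | 69% | 91% | 96% |
| 0.20 | 49% | 91% | 99% | >99% |
| 0.50 | 88% | >99% | >99% | >99% |

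Under this model more is recorded in the Tuina arm whenever p lies strictly between 0 and 1. The gap runs from large to negligible, depending on p and on how the teaching contacts are read. The table shows a direction and says nothing about the size in this trial.

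**The case against.** A reader might infer that the instruction suppresses harms, or that events after week 4 go unreported. The document does not support either.
- The instruction concerns the intervention and is directed only at the assessor. It is an ordinary blinding safeguard.
- No section makes the assessor the channel for adverse events. The assessor's remit is outcomes; safety is a separate section with the research team responsible, and recording runs for the whole trial.
- Nothing stops a participant telling the Tuina doctor, the staff who give guidance, or the investigators.
- Symptoms are not off limits at the visits. The WOMAC and the TCM symptom evaluation, at weeks 4, 8 and 16, ask about pain, function and swelling, so a knee flare would show in the scores.

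A reader might also take 11 against 3 as the measure of imbalance. That count leaves out the guidance and teaching contacts, which narrow the relative gap. Nor does the Statistical Analysis section state any between-arm test of harms. Finally, who asks about events, and in what words, commonly sits in a full protocol or case report form that an article condenses.

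Most of this stands, and it limits the point. Two things survive. The point does not rest on missing detail alone: a strict instruction without an exception is printed twice and sits badly with the safety section. And a flare that shows up in a WOMAC score is not an adverse-event record, which by the plan's own list needs timing, severity, duration, measures taken and outcome.

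**Conclusion.** The point holds as a risk and is not a demonstrated bias. The plan gives a broad non-disclosure instruction with no stated exception for harms, records events as observed, and gives one arm 8 more clinician contacts in weeks 1 to 4. Reporting may be discouraged at the evaluation visits, and ascertainment may differ between arms, with more events likely recorded under Tuina. The size cannot be determined from the document.

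This rests on three assumptions: that some participants read the instruction to include symptoms they attribute to treatment, that Tuina doctors note events they see or hear of, and that no arm-neutral enquiry is laid down elsewhere. It is a cheap improvement to the harms record and does not touch the primary comparison.

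**What to change.** 1. In Randomization, Allocation, and Blinding, and where the Discussion repeats the instruction, state that it does not cover symptoms or harms, and that these go to an existing unblinded member of the research team and not to the assessor.
2. In Safety Assessments, have that member ask both arms the same adverse-event question at weeks 4, 8 and 16, after the outcome assessment. This keeps the assessor blind.
3. If harms are compared between arms, use these common-schedule reports, and list events noticed only during Tuina sessions separately.

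**Cost.** One reworded instruction and one case-report-form question at three existing time points, with no added visits or staff. There is slightly more recording work, and recorded event rates may rise. Quality Assurance says the protocol will stay unaltered during the study, and the Abstract reports 69 of 96 participants enrolled by April 2025 (the Results section says 55). The change therefore needs a documented amendment. Events collected before it should be identified as such, since they were gathered under the existing instruction.

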### Intervention

We will explain the details of our study to the participants before they join our study.

#### Control Group (Conventional Treatment)

According to the “Basic treatment” part of the *Guidelines for TCM Diagnosis and Treatment of Knee Osteoarthritis* (2020 edition) [21], we will include health education, weight management, functional exercise, and self-administered acupressure [22]. We will distribute health education manuals, provide online and offline guidance for patients, popularize KOA-related health knowledge to patients, and help them understand the importance of daily KOA protective measures and precautions through popular science health education. In this group, patients will be taught self-administered acupressure and functional exercise once daily, 5 days/week for 4 weeks.

#### Self-Administered Acupressure

First, patients will form a claw-like shape with 1 hand and use it to squeeze the quadriceps muscle along the front of the thigh, moving along the pathways of the liver, spleen, stomach, and gallbladder meridians.

Second, they will use their fingers/thenar/hypothenar to press the acupoints (ST34, ST35, ST36, SP9, SP10, GB34, EX-LE2, and EX-LE4) briskly and then release with moderate pressure repetitively for about 1 minute per acupoint.

Third, they will rub their hands together until they become warm. Subsequently, they will place their hands around the knee joints and perform gentle, repeated kneading motions until the knee joints experience a sensation of slight warmth.

#### Functional Exercise

Participants will perform straight leg-raising exercises, 3-5 sets per day, with 10-15 repetitions per set. They will also perform wall squats, 3-5 sets per day, commencing with 30-60 seconds per squat and progressing to 90-120 seconds as muscle strength increases, with the knee angle maintained between 120°and 150°. Furthermore, they will perform knee flexion and extension resistance exercises, 3-5 sets per day, with 10-15 repetitions per set.

#### Intervention Group (Tuina Plus Conventional Treatment)

In this group, the treatment regimen will also receive Tuina therapy based on hip-knee-ankle synergy (Figure 2). The frequency of treatment will be twice a week for 4 weeks. We have established a scientific, normative, standardized work process, operating procedures, and quality standards. All treatment will be performed by registered Tuina doctors, who have clinician qualifications and have been engaged in Tuina clinical work for more than 5 years. All of have graduated with Tuina as their major and have been trained and assessed with Tuina's standard operating procedures (SOP) for this study.

First, the patient will lie in a supine position, with legs straight and relaxed. The doctor will relax the soft tissues of the groin, thigh, knees, and lower legs in turn, including the quadriceps femoris muscle, the tibialis anterior muscle, and soft tissues around the patella. The degree of manual relaxation will be determined based on the patient’s sensation of slight soreness and distension.

Second, the patient will keep lying in a supine position. Acupressure will be administered to the points around the knee. The patella will be mobilized, and the cordage, patellar ligament, medial and lateral retinaculum, and medial and lateral collateral ligament will be relaxed. Depending on the actual situation, knee adjustment manipulation techniques in a seated or a supine position will be performed, when necessary. Next, the doctor will rub the knee and transfer heat.

Third, the patient will keep lying in a supine position. The doctor will hold the patient’s ankle with both hands and place the thumb on the lateral or medial malleolus suture and press, while the other 4 fingers will be fixed, rotating and shaking the foot several times. The ankle will be pulled outward and downward with both thumbs, and the ankle joint will be held and the lower limb stretched.

Finally, the patient will lie in a prone position, the doctor will relax the muscles of the buttocks, thighs, and calves in turn, including the gluteus maximus, gluteus medius, piriformis, biceps femoris, and gastrocnemius muscles. The handling will not be too heavy. The doctor will measure the degree of swelling and numbness. Depending on the actual situation, hip joint adjustment manipulation techniques will be performed, when necessary.

**Figure 2 figure2:**
[figure not shown]
Tuina therapy with hip-knee-ankle synergies: (a) Relax the muscles of the lower extremity (with emphasis on the region surrounding the knee), (b) perform arthrokinetic mobilization and adjustment of the knee, (c) perform arthrokinetic mobilization and adjustment of the ankle, and (d) perform arthrokinetic mobilization and adjustment of the hip.

### Outcome Measures

To enhance patient compliance and mitigate potential bias or data loss from frequent in-person visits, we have opted to evaluate WOMAC, Key Symptoms and Signs/TCM Syndrome Classification Quantitative Evaluation of KOA [21], and TSK-11 [23] scores at 4 time points (baseline and 4-, 8-, and 16-week follow-up), while assessing Functional Movement Screen (FMS) [24,25], Timed Up and Go (TUG) test [26,27], and Weight Bearing Lunge Test (WBLT) scores at 2 time points (baseline and 4-week follow-up).

#### Primary Outcome

##### Western Ontario and McMaster Universities Osteoarthritis Index

WOMAC [18,28] is a commonly used outcome measure for OA, and it will be applied at baseline and at 4-, 8-, and 16-week follow-up. WOMAC is composed of 24 items in 3 subscales (5 for pain, 2 for stiffness, and 17 for physical function). Each item is rated on a scale of 0-10 (with higher scores indicating worse pain, function, and stiffness), and total scores range from 0 to 240. WOMAC scores are classified as mild (<80), moderate (80-120), and severe (>120). Assessing the changes in WOMAC scores before and after the intervention will enable us to evaluate the specific effects of Tuina on pain relief and functional improvement in patients with KOA.

#### Secondary Outcomes

##### Key Symptoms and Signs/TCM Syndrome Classification Quantitative Evaluation of KOA

This evaluation focuses on assessing the degree of pain, swelling, and accompanying symptoms in patients with KOA. It will be used to evaluate the short- or midterm clinical efficacy of Tuina in KOA and will be applied at baseline and 4-, 8-, and 16-week follow-up. It. This will allow us to observe the effects of Tuina on KOA from a TCM perspective, offering a comprehensive understanding of its therapeutic effects.

